### Analyses

#### Randomisation check

A 2 (autonomy support: present or absent) x 2 (implementation intention: present or absent) MANOVA will be conducted, with baseline demographic, behavioural, and psychological measures as dependent variables, and the intervention components as the independent variables, to test for between-group differences across the intervention conditions at baseline.

#### Manipulation checks

As the effect of implementation intentions might be diminished by participants failing to comply with instructions consistent with the approach, we will content analyse participants’ implementation intention scripts (typed in response to the implementation intention manipulation) to ascertain the extent to which participants complied with the intervention instructions [33]. Independent raters familiar with implementation intentions will rate the quality of scripts based on the presence or absence of key planning components: (1) used the if-then format, (2) specified a relevant, realistic, and appropriate cue, (3) linked the cue to the desired response. A one-way independent groups ANOVA will be conducted to test the effect of autonomy support on goal self-concordance as a manipulation check.

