## Methods

### Design

The study will adopt a 2 (autonomy support: present vs. absent) x 2 (implementation intention: present vs. absent) design (see Fig. 1). Given evidence for the use of periodic prompts in supporting online interventions [83, 84] and the increased effectiveness of presenting reminders in implementation intention interventions [85] participants will be sent the components of their respective intervention via email following its conclusion. At follow-up, four weeks later, participants will be invited to complete the same theory-based measures as at baseline to assess the influence of the intervention in terms of changes in theoretical constructs and behavior.

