### Combined condition

Heckhausen and Gollwitzer’s [74] action-phase model places the predecisional (i.e., motivational) as preceding a behavioural decision, from which an individual passes through to the preactional (i.e., volitional) phase. Accordingly, participants in the combined condition will first receive the autonomy support component, followed by the implementation intention component. A conceptual map of the intervention components relative to the components in the action-phase model is included in Fig. 2.

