### Hypotheses

It is hypothesized that participants receiving both autonomy support and implementation intention components will exhibit greater reductions in pre-drinking alcohol consumption and alcohol-related harm at follow-up, relative to participants receiving either intervention component in isolation, in accordance with evidence supporting the combination of these approaches in potentially targeting two important components of the action-phase model [64, 75, 76].

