## Discussion

Pre-drinking is associated with significant risks attributable to excessive alcohol consumption [19, 20, 95]. No theory-based interventions to reduce pre-drinking alcohol consumption have yet to be developed. The present protocol has outlined a theory-based intervention that will attempt to reduce pre-drinking alcohol consumption and alcohol-related harm, by targeting the volitional and motivational phases of action, according to the action-phase model outlined by Heckhausen and Gollwitzer [74]. There is evidence that the provision of autonomy support is associated with greater autonomous motivation to engage in behaviour, and that autonomous motivations for reducing alcohol consumption are associated with reductions in alcohol consumption [33, 69]. Although, exhibiting motivation is a necessary but not sufficient condition for behavioural enactment [49, 96]. Forming implementation intentions has been shown to strengthen the link between intention and behaviour, by providing a link between a contextual cue and an intended response [35, 54]. Combining these approaches is based on the premise that promoting goal self-concordance is important in successful goal attainment [78], and is integral to the efficacy of implementation intention approaches [57, 79]. Therefore, an approach that combines the volitional and motivational action phases, providing individuals with autonomy supportive context for behaviour change and the regulatory skills with which to translate this motivational impetus into behaviour, may be more effective in eliciting successful behaviour change. We therefore expect that while participants in the autonomy support and implementation intention conditions will report lower pre-drinking alcohol consumption at follow-up, the combination of these approaches will see the greatest reduction in pre-drinking alcohol consumption. This is because individuals may be autonomously motivated and intend to reduce their pre-drinking alcohol consumption, let may lack the regulatory capacity required to translate this intention into action (i.e., inclined abstainers) [48]. Similarly, the formation of if-then plans to reduce pre-drinking alcohol consumption may not lead to action if the underlying rationale for these plans is not autonomous [79]. Providing autonomy support to facilitate autonomous motivation will form a sound basis for the development of if-then plans, leading to the translation of that motivational basis into successful action and greater reductions pre-drinking alcohol consumption.

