### Autonomy support condition

Participants are presented with a script comprising a series of statements using autonomy-supportive language, and given prompts to write about reasons pursuing the goal of reducing their pre-drinking alcohol consumption may be worthwhile:

“Over the next few weeks, we’d like you to consider reducing your pre-drinking alcohol consumption. Remember, when we talk about pre-drinking, we mean: drinking alcohol at home, or someone else’s house, prior to attending an event (where drinking alcohol may continue).

Pre-drinking can be harmful, so there are many good reasons why people might set themselves the goal of reducing their pre-drinking alcohol consumption. While we understand that this goal may not be overly enjoyable or interesting, if you identify reasons why reducing your pre-drinking alcohol consumption is important to you, you may feel you are more able to meet this goal. You are free to choose exactly how you will reduce your pre-drinking alcohol consumption – developing your own strategy that uses your set of skills and resources often leads to success.

The following prompts are to help you think of ways you can reduce your pre-drinking alcohol consumption, avoid negative outcomes associated with alcohol consumption, and gain the benefits of reducing pre-drinking alcohol.

You will be taken through these ways step-by-step; as you read, you will be provided with reasons for completing these prompts and how they might help you.

Remember, whether or not you engage in these exercises is entirely up to you - it’s your choice.

Example:

Identifying some of the negative consequences of pre-drinking can be a good first step in forming your plan to reduce your pre-drinking alcohol consumption. Reducing your alcohol consumption during pre-drinking sessions will help you to avoid some of these negative consequences you may experience when pre-drinking excessively.”

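### The autonomy-support manipulation check averages over the second factor, so it can be significant on the strength of the autonomy-only arm and says little about uptake in the combined arm

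*Protocol article*

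**What the plan says.** The Design section of the protocol article sets out a factorial trial: "The study will adopt a 2 (autonomy support: present vs. absent) x 2 (implementation intention: present vs. absent) design". The randomisation check, the two primary ANCOVAs and the MANCOVA on psychological variables are all written as 2 x 2 analyses. The check on autonomy support is not: "A one-way independent groups ANOVA will be conducted to test the effect of autonomy support on goal self-concordance as a manipulation check". It names no implementation-intention term, interaction or within-level contrast.

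The Hypotheses section is about one arm: "participants receiving both autonomy support and implementation intention components will exhibit greater reductions in pre-drinking alcohol consumption and alcohol-related harm at follow-up", compared with either component alone. In that arm the two tasks come in sequence: "participants in the combined condition will first receive the autonomy support component, followed by the implementation intention component". The only measurement point given after allocation is the follow-up: "At follow-up, four weeks later, participants will be invited to complete the same theory-based measures as at baseline". A post-intervention self-concordance score in the combined arm therefore comes after both components.

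**The concern.** A manipulation check is there to help interpret the outcome result. Here the outcome result of interest is the combined arm against each single component. The Discussion gives the reasoning: "Providing autonomy support to facilitate autonomous motivation will form a sound basis for the development of if-then plans". The useful question is therefore whether autonomy support raised self-concordance among people who also wrote if-then plans. The planned test does not isolate that group. If autonomy support took hold when given alone but not in the combined arm, the check could still be significant. A disappointing combined-arm result might then be put down to the combination, when one of its components had not taken hold there.

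**Working it through.** **Inputs.** The plan gives no power, effect size or alpha for this check, so there is no figure of its own to reproduce. From the Participants section: 196 / 4 = 49 per cell. The derivation of 196 is a separate matter; only the cell size is used here. Assumed: SD 1, alpha .05 (with .025 also shown for the planned test), and d from 0.3 to 1.0. The protocol's planning effect for the primary outcomes, f = .25, corresponds to d = 2 x .25 = 0.5 for two equal groups, but it is not stated for self-concordance.

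**What the test estimates.** Write the cell means as C (control), A (autonomy support only), I (implementation intention only) and AI (combined). With equal cells the one-way contrast is

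(A + AI)/2 − (C + I)/2 = ½[(A − C) + (AI − I)].

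This is the average of two simple effects. The 2 x 2 main effect of autonomy support is the same quantity.

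**Scenario.** C = I = AI = 0 and A = d, so autonomy support works alone and does nothing in the combined arm. Noncentrality parameters, with n = 49:

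- One-way: the contrast is d/2. Pooling unlike cells inflates the residual variance to 1 + d²/8, so λ = 49(d²/4)/(1 + d²/8). At d = 0.5: 3.0625/1.03125 = 2.97. At d = 0.8: 7.84/1.08 = 7.26.
- 2 x 2 main effect: λ = 49d²/4. At d = 0.5: 3.06. At d = 0.8: 7.84.
- 2 x 2 interaction: λ = d²/(4/49) = 12.25d², the same as the main effect in this scenario.
- Combined versus implementation intention alone: the true difference is 0, so it is significant at the nominal 5%.

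The last column below uses a different scenario, in which autonomy support has effect d in both strata. There the combined versus implementation-intention-alone contrast has λ = d²/(2/49) = 24.5d².

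| d | Planned one-way passes | 2 x 2 main effect passes | Interaction detects failure | Combined vs implementation intention alone, if effect is d in both strata |
|---|---|---|---|---|
| 0.3 | 18% | 18% | 18% | 32% |
| 0.5 | 40% | 41% | 41% | 69% |
| 0.65 | 60% | 62% | 62% | 89% |
| 0.8 | 77% | 80% | 80% | 98% |
| 1.0 | 91% | 94% | 94% | 99.8% |

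At alpha .025 the planned one-way check passes in 30% (d = 0.5), 49% (0.65), 67% (0.8) and 85% (1.0).

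**Simulation check** (20,000 runs each). The one-way test is significant in 40%, 78% and 92% of trials at d = 0.5, 0.8 and 1.0, close to the formula. It is significant while the combined-arm contrast is not in 38%, 75% and 89%.

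**Precision.** The standard error of the combined-arm contrast is √(2/49) = 0.20 SD, so its 95% interval is about ±0.40 SD. For the interaction it is √(4/49) = 0.29 SD, about ±0.56 SD.

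**Alternative reading.** If one-way meant four groups, the omnibus test would be significant in 71% of trials at d = 0.5 in the same failure scenario. That reading does not remove the difficulty.

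**The case against.** Four arguments carry weight.

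- **Averaging is conventional.** Asking whether a factor moved its target construct on average is an ordinary manipulation check. A reader might infer that the error lies in leaving out the second factor. The arithmetic does not support that: with equal cells the 2 x 2 main effect estimates the same quantity and passes slightly more often in the failure scenario. What is missing is the interaction and the within-stratum contrast. This objection stands as a limit on the point.
- **The MANCOVA may already help.** It is a 2 x 2 analysis that includes autonomous motivation. The Measures section describes one instrument under a heading naming both autonomous motivation and goal self-concordance, and defines only the relative score, so the two variables may share items or be the same score. A reader might infer that the MANCOVA offers no protection; that goes too far. Still, it tests six outcomes jointly, is not presented as a manipulation check and names no combined-arm contrast, so its help is partial.
- **The scenario is assumed.** No passage gives an effect on self-concordance or suggests exactly zero in the combined arm. At d = 0.5 the check fails more often than it passes, and the interaction does no better. The 77% should not be quoted without the range.
- **The check triggers nothing.** No decision rule hangs on it, the primary ANCOVAs do not use it, and the limitations in the Discussion rank mediating constructs below overall effects. This keeps the consequence moderate.

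A reader might also infer the same fault in the rating of if-then scripts, which serves "to ascertain the extent to which participants complied with the intervention instructions", because the autonomy-support script says "Remember, whether or not you engage in these exercises is entirely up to you". The documents do not support this. The section neither pools the two plan-writing cells nor rules out comparing them. The sentence in the script introduces that script's own prompts, and the autonomy-only arm reads it too.

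**Conclusion.** The point holds in a limited form. The stated check estimates an average effect, while the hypothesis needs to know what happened in the combined arm. If autonomy support fails only there, the check can still be significant: in about 40% of trials at d = 0.5, rising to 91% at d = 1.0. These figures rest on 49 completers per cell, unit SD, alpha .05 and a zero combined-arm effect, of which only the cell size comes from the protocol. They show what the test cannot distinguish; they do not predict that autonomy support will fail. The weakness affects the interpretation of a combined-arm result and leaves the primary analyses untouched.

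**What to change.** Replace the one-way ANOVA with a model for goal self-concordance containing autonomy support, implementation intention and their interaction. Report, each with a 95% confidence interval, the interaction and the autonomy-support effect within the implementation-intention cells (combined minus implementation intention alone). Do not rest the check on the autonomy-support main effect alone.

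Add one sentence of caution: at a medium effect (d = 0.5) the interaction has only about 41% power with 49 per cell, so a non-significant interaction will not be taken to show equal uptake. The within-stratum contrast is the more useful summary, with 69% power at d = 0.5 and 89% at d = 0.65 if autonomy support works equally in both strata.

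The cost is two or three sentences of analysis text. It uses scores already being collected and needs no extra participants.

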#### Effects of the intervention on pre-drinking alcohol consumption and alcohol-related harm

Two ANCOVAs (autonomy support: present or absent) x 2 (implementation intention: present or absent) will be conducted to ascertain the effect of the intervention on follow-up self-reported pre-drinking alcohol consumption, and summed B-YAACQ scores, at follow-up, controlling for baseline pre-drinking alcohol consumption.

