**Analyses:**

The main and interactive effects of the intervention components in reducing our primary dependent variables, namely, pre-drinking alcohol consumption and alcohol-related harm at four-week follow-up will be tested. Baseline alcohol consumption and demographic information will be included in the analysis as covariates.

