#### Alcohol-related harm

The Brief Young Adult Alcohol Consequences Scale (B-YAACQ) [93] is a validated measure of the experience of alcohol-related harm that is well-suited to use in college populations for the purpose of evaluating change in alcohol consequences. The measure comprises a series of 24 participant-endorsed yes/no statements related to alcohol-related harm (e.g., “*I have felt very sick to my stomach or thrown up after drinking”*). Scores are derived from summing all *yes* responses to create a unidimensional index of alcohol-related harm [93]. Participants will complete the B-YAACQ at baseline and follow-up, to ascertain the effects of the intervention in reducing alcohol-related harm attributable to reductions in pre-drinking alcohol consumption. The time-frame of the B-YAACQ will be modified to refer to harm from alcohol consumption in the previous four-week period, to give a fine-grained view of the effects of the intervention on alcohol-related harm (see [94]).

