### Participants

Eligible participants will be current undergraduate students who regularly consume alcohol (i.e., are current ‘drinkers’), and have engaged in pre-drinking behaviour within the previous six months. Based on medium effects for implementation intentions on reductions in alcohol consumption reported in Hagger, Lonsdale [33] and the meta-analysis of self-determination theory applied to health contexts reported in Ng et al. [62], we conducted a statistical power analysis using G*Power to ascertain an adequate sample size for the intervention. Specifically, the power analysis was for an Analysis of Covariance (ANCOVA) on the two key dependent variables, alcohol consumption and summed B-YAACQ scores, with the intervention groups as the independent variables powered to detect a medium effect size (Cohen’s *f* = .25) with power set at .80 and alpha set at .025, and baseline scores on the dependent variable as a covariate. The analysis yielded 196 participants (i.e., 49 per group) for each analysis.

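### The harm ANCOVA adjusts for baseline pre-drinking, while the power section assumes the outcome's own baseline; the collected baseline B-YAACQ goes unused, probably at a cost in precision

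*Protocol article*

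**What the plan says.** Four places in the protocol article bear on the covariate for harm.

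- **Abstract, Analyses.** Harm is one of "our primary dependent variables, namely, pre-drinking alcohol consumption and alcohol-related harm at four-week follow-up". On adjustment: "Baseline alcohol consumption and demographic information will be included in the analysis as covariates". Baseline harm is not named.
- **Methods, Participants (sample size).** The power analysis is for an ANCOVA "on the two key dependent variables, alcohol consumption and summed B-YAACQ scores", with "baseline scores on the dependent variable as a covariate". It uses f = .25, power .80 and alpha .025, and arrives at 196 participants (49 per group) for each analysis.
- **Measures, Alcohol-related harm.** "Participants will complete the B-YAACQ at baseline and follow-up", with the time frame changed to the previous four weeks.
- **Analyses, Effects of the intervention on pre-drinking alcohol consumption and alcohol-related harm.** Two factorial ANCOVAs are planned, on follow-up consumption "and summed B-YAACQ scores, at follow-up, controlling for baseline pre-drinking alcohol consumption".

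**The concern.** For consumption, the sample-size paragraph and the analysis section name the same covariate. For harm they do not: one implies the baseline B-YAACQ, the other names baseline pre-drinking. An analyst cannot follow both, and an open covariate choice on a primary outcome can end up being settled after the data are seen.

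A score measured twice, four weeks apart and over windows of the same length, would usually predict itself better than a different variable predicts it. If that holds here, leaving out the baseline B-YAACQ leaves more residual variance in the harm model, so wider intervals and less power than the power section's model would give. The data needed to avoid this are already being collected.

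**Working it through.** **1. The plan's own figure.** Inputs from Participants: f = .25, alpha = .025, power = .80, four groups, one covariate. The G*Power ANCOVA calculation uses a noncentral F with λ = f²N and denominator df = N − 4 − 1. The N required is:

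| Numerator df | N for power .80 | Power at N = 196 |
|---|---|---|
| 1 (main effect or interaction) | 155 | .892 |
| 2 | 188 | .820 |
| 3 (four-group test) | 212 | .762 |

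None of these returns 196, and using 0, 1 or 2 covariates leaves N unchanged. The article does not state the numerator df. The present point does not rest on reproducing 196. The table does show that .89 is the computed power of a 1-df test at 196, not a figure the plan states; its target is .80.

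**2. Effect of swapping the covariate.** Residual variance after adjustment is proportional to 1 − r², where r is the covariate's correlation with follow-up B-YAACQ. If f = .25 is defined on the residual scale of the own-baseline model, the effective f in the planned model is

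f_eff = .25 × √[(1 − r_own²) / (1 − r_pre²)].

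The article gives neither correlation. **Assumed:** r_own = .5 to .7 (baseline B-YAACQ) and r_pre = .2 to .4 (baseline pre-drinking). Example at .6 and .3: the variance ratio is (1 − .09)/(1 − .36) = .91/.64 = 1.42, and f_eff = .25 × √(.64/.91) = .210.

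| r_own, r_pre | Residual variance ratio | f_eff | 1-df power at 196 | N for .80 |
|---|---|---|---|---|
| .5, .4 | 1.12 | .236 | .852 | 173 |
| .5, .2 | 1.28 | .221 | .797 | 198 |
| .6, .3 | 1.42 | .210 | .750 | 219 |
| .7, .4 | 1.65 | .195 | .680 | 254 |
| .7, .2 | 1.88 | .182 | .615 | 289 |

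Against .892 with the own-baseline covariate, the middle case is like losing about 30% of participants (1 − .64/.91 = .30).

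**3. The other reading of f.** If f = .25 is on the unadjusted scale, any covariate only helps: f_eff = .25/√(1 − r²). With pre-drinking at r = .2, .3 and .4, 1-df power at 196 is .904, .920 and .940. With no useful covariate (r = 0) it is .892. Own-baseline adjustment would give .962 to .996 for r = .5 to .7. On this reading the planned model is still less efficient than it could be, but it clears the target.

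**The case against.** The strongest reply accepts the mismatch and disputes its consequence.

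- **The sample size does not depend on the covariate.** G*Power takes f directly and charges a covariate one degree of freedom, so 196 would be the same either way. The article takes f from medium effects in cited work and never says that it is a residual-scale value. This stands. A reader might infer that the trial is under-powered for harm; the article does not support that. Even on the residual-scale reading, one assumed pair gives .85 and another .80 to two decimals. The 3-df test is at .76 before any covariate change, which is a separate matter.
- **Pre-drinking may not be the only covariate.** The abstract adds demographics. This stands, although demographics do not replace the baseline of the outcome itself.
- **The choice may be deliberate.** The abstract, the primary ANCOVAs and the MANCOVA on psychological variables all adjust for baseline drinking, so the power paragraph is the outlier. Adjusting for a prespecified baseline variable is valid. This explains the choice but does not reconcile the sections.
- **No bias follows.** A reader might infer that chance imbalance in baseline harm biases the estimate. Randomisation keeps it unbiased in expectation, and such imbalance is already reflected in the larger standard error, so it is the same precision loss seen from another side. Its size is also easy to overstate. A 1-SE imbalance is √(2/49) = .20 SD between two cells but √(2/98) = .14 SD for a main effect. With slopes of .5 to .7 this moves the estimate by .10 to .14 SD or .07 to .10 SD respectively, before the part that adjusting for pre-drinking removes.

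**Conclusion.** The inconsistency is certain and confined to the harm outcome: the power section describes an own-baseline model, the analysis section and abstract describe another, and the baseline B-YAACQ is collected without a role in the primary harm analysis. The planned analysis is valid and unbiased under randomisation. It is probably less precise than the one the power section describes, provided the baseline B-YAACQ predicts its follow-up better than baseline pre-drinking does.

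The size cannot be fixed from the article. On the residual-scale reading of f and the assumed correlations, 1-df power at 196 falls from .89 to between .85 and .62; on the unadjusted reading it stays at or above .89. Power below .80 is possible, not demonstrated. This should be fixed before analysis, but it does not invalidate the trial's harm comparison.

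**What to change.** In the analysis section, state that each ANCOVA adjusts for the baseline of its own outcome: baseline pre-drinking consumption for consumption, and the baseline four-week B-YAACQ score for harm. Baseline pre-drinking may stay in the harm model as a second covariate. Bring the abstract's list of covariates into line, and say whether demographics enter the primary models, so that abstract, sample-size paragraph and analysis section describe one model per outcome.

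Cost: one sentence in the analysis section with a matching edit to the abstract, at most one degree of freedom, and no new data.

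### For alcohol-related harm, the analysis section adjusts for baseline pre-drinking while the power paragraph assumes the outcome's own baseline, and baseline B-YAACQ, although collected, is named in no harm model

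*Protocol article*

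**What the plan says.** Four places in the protocol article bear on the covariates of the two outcome ANCOVAs.

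- **Analyses, effects on consumption and harm.** Two 2 x 2 ANCOVAs are planned, one on follow-up pre-drinking consumption and one on "summed B-YAACQ scores, at follow-up, controlling for baseline pre-drinking alcohol consumption". Baseline pre-drinking is the only covariate named, and it serves both models.
- **Participants (power analysis).** The calculation covers the "two key dependent variables, alcohol consumption and summed B-YAACQ scores", with "baseline scores on the dependent variable as a covariate". Read outcome by outcome, this is baseline consumption for consumption and baseline B-YAACQ for harm.
- **Abstract, Analyses.** The two outcomes are called "our primary dependent variables, namely, pre-drinking alcohol consumption and alcohol-related harm at four-week follow-up". The next sentence reads: "Baseline alcohol consumption and demographic information will be included in the analysis as covariates". Baseline harm is not mentioned, and the demographic variables are not listed.
- **Measures, Alcohol-related harm.** "Participants will complete the B-YAACQ at baseline and follow-up", and the recall period is changed to the preceding four weeks.

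**The concern.** The harm ANCOVA described in the power paragraph is not the one described in the analysis section, and harm is a primary outcome. This is not detail left to a fuller document: the article states the covariate in more than one place, and the statements disagree.

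Two things are at stake.

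- **Prespecification.** If the sections stay unreconciled, the harm model could be run with baseline pre-drinking, with baseline B-YAACQ, or with either plus demographics, and each choice could be defended from the text.
- **Precision.** A baseline measurement on the same instrument and recall window usually predicts the follow-up score better than a related behaviour does. If that holds here, the written model has a larger residual variance than it needs, and any chance difference between arms in baseline harm stays unadjusted in the estimate. The hypotheses concern reductions in harm, which makes baseline harm the natural quantity to condition on.

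**Working it through.** **Step 1. The covariates side by side**

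| Section | Consumption model | Harm model |
|---|---|---|
| Participants (power) | baseline consumption | baseline B-YAACQ (implied by the general phrase) |
| Analyses | baseline consumption | baseline consumption |
| Abstract | baseline consumption + demographics | baseline consumption + demographics |

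The Participants and Analyses sections agree for consumption and conflict for harm. The abstract's demographics are a separate mismatch that touches both models.

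**Step 2. The plan's own figure**

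Stated inputs: f = .25, alpha = .025, power = .80, four groups, one covariate, N = 196. The G*Power form for ANCOVA uses noncentrality lambda = N x f^2 and denominator df = N - groups - covariates. The numerator df is not stated. The required N is 155 for 1 df, 188 for 2 df and 212 for 3 df, so 196 is not reproduced. That is a different point, and nothing below depends on it.

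At N = 196, lambda = 196 x 0.0625 = 12.25 and denominator df = 196 - 4 - 1 = 191. Power is .89 for 1 df and .76 for 3 df. The main results below use 1 df, because each main effect and the interaction in a 2 x 2 design has 1 df.

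The formula uses the number of covariates, not their identity. Swapping baseline pre-drinking for baseline B-YAACQ leaves the formula N unchanged.

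**Step 3. Residual variance**

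The article gives no correlations. Assumed correlations with follow-up B-YAACQ:

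- baseline B-YAACQ (own): r = 0.5, 0.6, 0.7
- baseline pre-drinking (cross): r = 0.2, 0.3, 0.4

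Residual variance is proportional to 1 - r^2. Own baseline gives .75, .64, .51; cross gives .96, .91, .84. The ratio of written model to own-baseline model runs from .84/.75 = 1.12 to .96/.51 = 1.88. The middle pair gives .91/.64 = 1.42, an information loss of 1 - 1/1.42, about 30%.

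**Step 4. Power at N = 196, 1 df, alpha .025, on two readings of f = .25**

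*Reading A: f is on the residual scale after own-baseline adjustment.* Own-baseline power is .89. Under the written model, f becomes .25 x sqrt[(1 - own r^2)/(1 - cross r^2)].

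| Own r | Cross r | Variance ratio | f as written | Power as written |
|---|---|---|---|---|
| .5 | .2 | 1.28 | .221 | .797 |
| .5 | .3 | 1.21 | .227 | .82 |
| .5 | .4 | 1.12 | .236 | .85 |
| .6 | .2 | 1.50 | .204 | .73 |
| .6 | .3 | 1.42 | .210 | .75 |
| .6 | .4 | 1.31 | .218 | .79 |
| .7 | .2 | 1.88 | .182 | .62 |
| .7 | .3 | 1.78 | .187 | .64 |
| .7 | .4 | 1.65 | .195 | .68 |

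*Reading B: f is on the unadjusted SD scale.* The effective f is .25/sqrt(1 - r^2). Power as written is .90, .92, .94 for cross r = .2, .3, .4. With own-baseline adjustment it is .96, .98, .996 for r = .5, .6, .7.

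For a 3-df test the ordering is the same. Reading A gives .43 to .70 as written against .76; reading B gives .78 to .84 against .89 to .98.

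**The case against.** The case for leaving the model alone has real substance.

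- **The covariate may be deliberate.** The MANCOVA on psychological variables also uses baseline pre-drinking, and the article presents harm as following from pre-drinking. On that view the analysis section is a defensible model and the power paragraph is loosely worded. This is possible, but the two sections would still need reconciling, and own-baseline adjustment would still be the more precise choice under the assumed correlations.
- **There is no bias.** This stands. Under randomisation the written ANCOVA is unbiased in expectation, and chance imbalance in baseline harm is part of the sampling error that the standard error reflects.
- **The sample size does not move.** This stands. Both sections use one covariate, so the formula N is the same.
- **Baseline B-YAACQ is not necessarily unused.** This stands too. The randomisation-check MANOVA covers baseline behavioural measures and may include it. That check would describe an imbalance, not adjust for it.

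A reader might infer that the trial is underpowered for harm. That needs reading A, and the Participants section says only that the study is "powered to detect a medium effect size" drawn from earlier literature, without stating the scale or a covariate correlation. On reading B the written model exceeds .80 for a 1-df test. A reader might also infer that both primary models are in conflict, or that the strongest predictor of harm has been omitted. The first is wrong for consumption as between the Participants and Analyses sections. The second is plausible but is not shown anywhere in the article.

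**Conclusion.** The contradiction is confirmed from the text. For B-YAACQ, the analysis section and the power paragraph name different covariates, and no section names baseline B-YAACQ in the harm model although the score will be in hand. The abstract's unlisted demographics are a second, smaller inconsistency affecting both models.

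The consequences are an outcome model that is not uniquely fixed, lost precision, and unadjusted chance imbalance in baseline harm. The size of the loss, a residual variance 1.12 to 1.88 times larger, rests wholly on the assumed correlations. Its direction holds whenever baseline B-YAACQ correlates more strongly with follow-up B-YAACQ than baseline pre-drinking does. The effect on power depends on a scale for f that the article does not give, so failure to reach .80 is not established.

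This should be fixed before analysis because it concerns a primary test and the remedy is nearly free. It is not a validity failure.

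**What to change.** In the Analyses section, state that each ANCOVA adjusts for the baseline value of its own outcome: baseline pre-drinking consumption for follow-up consumption, and baseline B-YAACQ for follow-up B-YAACQ. Baseline pre-drinking may stay in the harm model as a second covariate if the investigators want it.

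Then use one covariate list in the abstract, the power paragraph and the Analyses section, either naming the demographic variables or removing them.

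The cost is a sentence or two of wording and, if the second covariate is kept, one degree of freedom (191 to 190 at N = 196, with no material effect on power). No new data are needed, and the formula sample size does not change.
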